### Feasibility

The pilot study was conducted over an eight month period in a unit with 3400 deliveries a year. We received approval from the Edinburgh multi-centre research ethics committee (MREC) and approval of the UK MHRA in keeping with the requirements of the EU directive on Clinical Trials. The obstetricians, anaesthetists, midwives, theatre staff and hospital pharmacist were very supportive. We received a high level of support from women undergoing caesarean section, the majority of who were happy to participate in the trial. There were no serious unexpected adverse events. The recruitment is summarised in the Consort flow chart. (Figure 1)

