### Governance issues

#### Ethical Committee Permission

Full ethical approval has previously been received for an eight- month local pilot study designed to develop the trial documentation and to test early feasibility issues.

05/MRE10/20 Approval date 16.03.05 MREC for Scotland

Ethical committee approval (Clinical Trials approved Committee) from the Coombe Women's Hospital, the National Maternity Hospital and the Rotunda Hospital, and approval of the Irish Medicines Board have been granted for this study.

IMB Application date 12.03.07 Approval date 27.04.07

Clinical trials approved committee Approval date 29.11.07

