### Safety considerations

Serious or unexpected serious adverse reactions (SUSARs) will be recorded and reported using the IMB approved SUSAR form. SUSARs include maternal death, surgery (other than caesarean section) in the 2 weeks following randomisation, transfusion of over 4 units of blood, admission to intensive care unit or suspected drug reactions. In the event of a SUSAR the form will be completed by the local trial co-ordinator and faxed to the trial co-ordinating centre at the Coombe Women's Hospital within 72 hours. From there the copies of the form will be sent to the trial statistician for unblinding and the chair of the Data Monitoring and Ethics Committee (DMEC). The IMB, the trial sponsor and the Chair of the MREC will also be informed by the DMEC Chair if considered appropriate.

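### The safety-reporting rule leaves notice of SUSARs to the regulator and the ethics committee to the DMEC Chair's discretion, and names the pilot's Scottish committee instead of the Irish committee that approved this trial

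*Protocol article*

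**What the plan says.** The Safety considerations section sets out the route in four steps.

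- **Form.** Events "will be recorded and reported using the IMB approved SUSAR form".
- **Scope.** "SUSARs include maternal death, surgery (other than caesarean section) in the 2 weeks following randomisation, transfusion of over 4 units of blood"; the list then adds intensive-care admission and suspected reactions to a drug.
- **First transmission.** The local co-ordinator completes the form, which is "faxed to the trial co-ordinating centre at the Coombe Women's Hospital within 72 hours".
- **Onward transmission.** "From there the copies of the form will be sent to the trial statistician for unblinding and the chair of the Data Monitoring" (that is, the DMEC). The last sentence then reads: "The IMB, the trial sponsor and the Chair of the MREC will also be informed by the DMEC Chair if considered appropriate".

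On approvals, the Feasibility section says of the pilot: "We received approval from the Edinburgh multi-centre research ethics committee (MREC"). Ethical Committee Permission opens with "Full ethical approval has previously been received for an eight- month local pilot study" and gives the reference "05/MRE10/20 Approval date 16.03.05 MREC for Scotland". It then lists separate approvals for the present trial: a Clinical Trials approved Committee, covering the Coombe, the National Maternity Hospital and the Rotunda (29.11.07), and the IMB (27.04.07).

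**The concern.** The regulator and the approving ethics committee authorised this trial, and both need to learn of the events that the protocol itself ranks as most serious. As worded, neither is certain to. The regulator is told on a judgement. The ethics notice depends on the same judgement and is addressed to a committee that, on this document, approved only the pilot.

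The stake is patient safety and oversight, not inference. The DMEC section provides yearly meetings, no formal interim analysis for safety or effectiveness, and no formal stopping rules. Reports of individual serious events are thus an important way for a signal to reach bodies outside the trial's own committees, and the rule that governs them should be firm and correctly addressed.

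**Working it through.** No arithmetic applies. The check is to follow every mention of the SUSAR route, the IMB, the MREC, the competent authority and the ethics committee through the article.

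**1. Who receives a report for certain?**

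| Recipient | Source | Conditional? |
|---|---|---|
| Co-ordinating centre (Coombe) | Safety considerations | No |
| Trial statistician | Safety considerations | No |
| DMEC chair | Safety considerations | No |
| DMEC as a body (all adverse events) | DMEC section | No |
| Trial Steering Committee, through the DMEC | DMEC section | No |
| IMB | Safety considerations, last sentence | Yes |
| An ethics committee (named as the MREC) | Safety considerations, last sentence | Yes |
| Irish committee that approved this trial | Not named in the safety route | Not provided for |

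The last sentence does not say who judges what is appropriate, but it names no actor other than the DMEC Chair.

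**2. Does another section supply a firm route to the IMB or the approving committee?** The only other commitment to notify them is in Trial end, where completion of the trial is to be notified to the competent authority and the ethics committee with no condition. Read together, the two sections make an administrative closure certain to reach these bodies and a maternal death not certain to.

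**3. Which committee is the MREC?** Apart from the safety sentence, the abbreviation stands only for the Edinburgh committee (Feasibility), recorded as the one for Scotland (Ethical Committee Permission). Both entries concern the pilot. The present trial's ethics approval is listed separately under a different committee. The safety sentence and the approvals section therefore do not match.

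**4. What does the list contain?** It mixes two kinds of event. Suspected drug reactions are one kind. Further surgery, transfusion of more than 4 units and intensive-care admission are serious events that can follow haemorrhage, which is the trial's own outcome, and need not be suspected or unexpected reactions. Maternal death stands on the same list. The discretion applies to all of them alike.

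**The case against.** The strongest case on the other side has four parts.

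- **Events do not vanish.** The DMEC receives all adverse events and passes them to the Trial Steering Committee, which has overall supervision and meets at least six-monthly. This stands. A reader might infer that a maternal death could stop at the DMEC Chair; the documents do not support that. What remains is that neither body is the regulator or the approving ethics committee.
- **The sentence can be read more kindly.** The form is an IMB-approved one, and the closing sentence speaks of the IMB and others also being informed, so it might describe an extra contact by the Chair on top of ordinary reporting. This is possible, but the text describes the form and never names the IMB as its recipient. If every form was meant to go to the IMB, the section does not say so and needs correcting on that ground.
- **Some triage is sensible.** Given the mixed list, forwarding every listed event as a SUSAR would be wrong. This stands and shapes the fix. It does not justify the same discretion over maternal deaths and suspected reactions.
- **MREC is probably a leftover label.** The national survey section says that the trial was first planned for Scotland. That explains the mismatch without removing it. A reader might infer that reports would in fact be sent to Scotland; that is more than an abbreviation can prove. The documents show only that the named recipient does not match the approving committee.

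Three further inferences are tempting and should not be drawn. First, the sentence also lists the sponsor, but the text at hand does not identify the sponsor; if it were the co-ordinating hospital, it would already hold every form. Second, only the site-to-centre step has a time limit, but an article may leave later deadlines to the full protocol. Third, the number of women recruited between yearly DMEC meetings would measure recruitment, not reports missed, and forms go to the DMEC chair outside that meeting cycle.

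**Conclusion.** The point holds as a defect in a stated rule. Notice to the IMB and to an ethics committee of events called SUSARs, including maternal death and suspected drug reactions, is conditional; the ethics recipient named is the pilot's; and no section assures notice to the Irish committee that approved this trial. Because the rule states an explicit condition and names a recipient, the article's brevity does not explain it away.

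Its reach is every event on the section's list. No event count can be put on it from the document, and the sample size, power, estimand and analysis are untouched. Since the DMEC and the Trial Steering Committee are informed without condition, this should be fixed but does not amount to a breakdown of oversight.

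The conclusion assumes that MREC has one meaning throughout the article, and that no fuller safety procedure, not shown here, overrides the printed rule.

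**What to change.** Change the wording of Safety considerations in three places.

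1. Replace the reference to the MREC chair with the Irish Clinical Trials approved Committee that approved this trial, so that the section agrees with Ethical Committee Permission.
2. Remove the DMEC Chair's discretion. State that the co-ordinating centre or the sponsor always sends suspected unexpected serious adverse reactions and maternal deaths to the IMB and to that committee. Keep the DMEC Chair as a parallel recipient.
3. List further surgery, transfusion of more than 4 units and intensive-care admission separately as serious events. State that assessment of causality and expectedness decides which of them are forwarded as SUSARs.

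The cost is a protocol wording change and a few extra notifications. Recruitment, treatment and analysis do not change.

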## Discussion

### Potential and Implementation of the findings

It is both important and timely that we evaluate the optimal approach to the management of the third stage at elective caesarean section. The caesarean section rate has risen dramatically over the last two decades and continues to rise. Safe operative delivery is now a priority and a reality for many pregnant women. Obstetricians, obstetric anaesthetists, midwives and pregnant women need high quality evidence on which to base management approaches. The use of oxytocin in this context is a poorly evaluated component of obstetric care. The overall aim is to reduce maternal haemorrhagic morbidity and its attendant risks at elective caesarean section. In addition we will develop a protocol establishing the economic implications and patient perspective of the two approaches.

### Dissemination

We aim to raise awareness of this clinical question and our proposed research approach at both local and national meetings. A final report will be prepared for the funding body and papers will be prepared for peer-review publication and national/international dissemination.
